#### Secondary study parameters

Secondary outcome parameters will be analysed with (G)LMMs, with the underlying distribution depending on the type of outcome variable and its distribution, in accordance with the above described analyses.

##### Exploration of interaction effects between timing and type of PTSD-treatment

We expect to have insufficient statistical power to detect statistically significant interaction effects between timing and type of PTSD-treatment. However, descriptive statistics of PTSD symptom severity (CAPS-5 scores) and treatment completion rates of all randomized groups will be presented (PE-simultaneous; EMDR-simultaneous; ImRs-simultaneous; PE-sequential; EMDR-sequential; ImRs-sequential), to explore whether there is anecdotal evidence for the existence such interaction-effects, which would be relevant for future research.

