### Sample size

First, we calculated the required sample size for the comparison between the three types of active PTSD treatments. Second, we calculated whether that sample size will provide sufficient power to compare the two timings of PTSD treatment. Three pairwise comparisons will be conducted between the active treatment arms (ImRs vs. PE, ImRs vs. EMDR; PE vs. EMDR). To detect a small-to-medium effect size (f = 0.15) in a pairwise comparison of pre-post change between two active treatment arms, with Bonferroni-corrected alpha = 0.0167, power = 0.85 and within-person correlation coefficient = 0.60, 54 participants are needed per arm. To make three pairwise comparisons 3 * 54 = 162 participants are needed. The allocation ratio between sequential and simultaneous PTSD treatment is 1:3. With *n* = 41 in sequential treatment and *n* = 121 in simultaneous treatment, power is 99% to detect a small-to-medium effect size (f = 0.15) in a comparison of pre-post change between simultaneous and sequential treatment, with alpha = 0.05, and within-person correlation coefficient = 0.60. To detect a small effect (f = 0.10) power is 81%. We expect 20% of the participants to drop out of the study, therefore in total 204 participants will be included in the study.

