### Data analyses

All analyses will be conducted on an intention-to-treat basis. To compare types and timing of PTSD treatment, (Generalized) Linear Mixed Models ((G)LMMs) will be used to model the primary and secondary outcome measures, with the underlying distribution (e.g., normal, gamma, (negative) binomial) depending on the type of outcome variable and its distribution. Next to these analyses based on classical statistics, a (hierarchical) Bayesian approach will be used to model the outcome parameters so that the relative evidence for the null-hypothesis (no differential effects) and the alternative hypothesis can be estimated. Prior distributions have been specified.

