##### Objective 3: head-to-head comparison PTSD treatments, regardless of timing of treatment

The 3 treatment conditions will be compared head-to-head (PE vs EMDR; PE vs ImRs; EMDR vs ImRs) with (G)LMMs. Baseline CAPS-5 score will be included as covariate and treatment type as a fixed effect. Overall effects will be evaluated, as well as between-group differences at separate follow-up time points, by adding time and an interaction between group and time to the model. The intercept will be treated as a random effect.

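### The exploration of a type-by-timing interaction rests on descriptive figures for six groups, three of them with about 14 to 17 patients, and names no interaction contrast or interval

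*Protocol article*

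**What the plan says.** The section Exploration of interaction effects between timing and type of PTSD-treatment first concedes that power for a significant interaction is expected to be insufficient. It then says that "descriptive statistics of PTSD symptom severity (CAPS-5 scores) and treatment completion rates of all randomized groups will be presented", naming the six combinations of therapy and timing. The stated purpose is "to explore whether there is anecdotal evidence for the existence such interaction-effects, which would be relevant for future research". No interaction estimate, interval or criterion is given.

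Elsewhere the article plans tools that could supply an estimate. For Objective 3, "Baseline CAPS-5 score will be included as covariate and treatment type as a fixed effect" in a mixed model; Objective 2 has the same structure with timing as the fixed effect. The opening of Data analyses adds a Bayesian approach "so that the relative evidence for the null-hypothesis (no differential effects) and the alternative hypothesis can be estimated".

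**The concern.** Evidence for an interaction is a statement about a contrast of contrasts: whether the simultaneous-minus-sequential difference is larger for one therapy than for another. A table of six group summaries does not give that contrast or its precision, and the three sequential groups are small. Low power is a good reason not to lean on a p-value. It is not a reason to leave out the estimate and its uncertainty, which matter most when power is low.

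Objective 2 pools over therapy type and Objective 3 pools over timing. This exploration is the only stated look at whether that pooling hides a difference. What is at stake is a hypothesis for future research that may be noise, and the absence of a stated range of interaction sizes that the data still allow. The primary comparisons are not affected.

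**Working it through.** **Inputs from the article.** Sample size: f = 0.15, alpha 0.0167, power 0.85, within-person correlation 0.60 and 54 per arm; "To make three pairwise comparisons 3 * 54 = 162 participants are needed"; "With *n* = 41 in sequential treatment and *n* = 121 in simultaneous treatment"; 20% dropout; 204 in total. Randomization and procedure: allocation of 1/4 to each first-stage group, then 1/3 to each therapy within the sequential group.

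**The plan's own figure.** The test is the group-by-time interaction for two groups and two measurements, with noncentrality λ = f²·N·m/(1 − ρ) = 0.0225 × 108 × 2 / 0.4 = 12.15 on (1, 106) degrees of freedom. At alpha 0.0167 the power is 0.852, against 0.85 stated. Inflating for dropout, 162/0.8 = 202.5, or 203, against 204. Both reproduce.

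**Group sizes.**
- Randomized: 204/4 = 51 per simultaneous group; 51/3 = 17 per sequential group.
- Analysable: 121/3 = 40.3 and 41/3 = 13.7 (sum 54, the stated number per therapy).

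**Precision of an interaction contrast.** Take an outcome SD of 1 in every group. The timing effect for one therapy has SE √(1/n_sim + 1/n_seq), and the difference between two therapies' timing effects has SE √(2/n_sim + 2/n_seq).
- 51/17: 0.280 SD and √(0.0392 + 0.1176) = 0.396 SD.
- 40.3/13.7: 0.313 SD and √(0.0496 + 0.1463) = 0.443 SD.

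**What chance alone produces.** The apparent interaction is taken as the range of the three timing effects at one visit. Simulation of 1,000,000 trials with normal outcomes and no true interaction gives:

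| Largest gap between therapies | 51/17 | 40.3/13.7 |
|---|---|---|
| Median | 0.44 SD | 0.50 SD |
| Above 0.3 SD | 73% | 78% |
| Above 0.5 SD | 42% | 49% |
| Above 0.8 SD | 11% | 17% |

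As a check, the median range is about 1.59 times the SE of one timing effect: 1.59 × 0.280 = 0.445 and 1.59 × 0.313 = 0.498.

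**Dependence on the reading rule**, still with no interaction:
- The rank order of the therapies differs between timings in 83% of trials if the therapies are equal (1 − 1/3! = 0.833), and in 53–58% if they truly span 0.5 SD.
- The timing effects do not all point the same way in 75% of trials if there is no timing effect, 37–42% if it is 0.3 SD and 11–16% if it is 0.5 SD.
- The largest gap in completion reaches 20 points in 40–63% of trials, assuming a true completion rate of 50–80%.

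**With baseline adjustment.** A correlation of 0.60 gives a residual SD of √(1 − 0.36) = 0.8. The contrast SE becomes 0.8 × 0.396 = 0.317 or 0.8 × 0.443 = 0.354, so the 95% half-width is 1.96 × 0.317 = 0.62 SD or 1.96 × 0.354 = 0.69 SD. The chance of a gap above 0.5 SD falls to 25–34%.

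**Power of a formal test.** If one therapy's timing effect differs by 0.5 SD, a 2-df interaction test has 20–24% power unadjusted and 29–35% with baseline adjustment.

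**The case against.** The section is candid. It admits insufficient power, promises only to present descriptive figures, and limits the result to anecdotal evidence for future research. No test, conclusion or recommendation follows from it. Objectives 2 and 3 are explicitly marginal and do not depend on it. A descriptive table in an openly underpowered exploration is accepted practice, and the 20–24% power supports the decision not to plan a formal test. If the table carries n, mean and SD, a reader could compute the unadjusted contrasts. All of this stands, and it makes the point an improvement rather than an error.

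Three stronger readings are tempting, and the article does not support them:
- A reader might infer that a false interaction would appear most of the time. That is not a property of the plan, which sets no reading rule. It holds for lenient readings, such as any change in rank order among equal therapies or a gap above 0.3 SD. It fails for a one-visit gap above 0.5 SD (42–49%) and clearly fails above 0.8 SD (11–17%).
- A reader might infer that the trial will report one therapy as better suited to one timing. The section says nothing of the kind.
- A reader might infer that the CAPS-5 figures will be unadjusted, or shown without any measure of spread. The section says neither, and a condensed article may leave this to the fuller documents.

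What remains is that the article states both a method and the inference to be drawn from it, and the method does not yield the quantity that the inference needs.

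**Conclusion.** The point holds in a limited form. Inspecting six group summaries, three of them from about 14 to 17 patients, cannot separate interaction from chance: with no interaction, the largest gap between therapies is typically about 0.45 to 0.5 SD at one visit. This rests on equal SDs, normal outcomes and the group sizes implied by the sample size section. The completion figures also rest on an assumed true rate of 50–80%. The frequency of a false reading cannot be fixed at one value, because the plan gives no rule. The low power is acknowledged and no stated figure is wrong. Reporting the contrast with its interval is the better method, and the models for it are already planned.

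**What to change.** In the section on exploring interaction:
- Add a type-by-timing term, together with both main effects, to the planned baseline-adjusted CAPS-5 mixed model, and report it at T2 and T3.
- Add the same term to a logistic model for completion.
- Report the three pairwise interaction contrasts with 95% intervals, and the Bayes factor from the Bayesian analysis already planned.
- Keep the six-group table as description only, and say that differences between cells will not be read as evidence of interaction unless the contrast supports it.

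The cost is an extra model term per outcome, a prior for it if none has been specified, and a few sentences of text. No further patients or data are needed. The downside is wide CAPS-5 intervals, about ±0.6 to 0.7 SD per contrast if the residual SD is 0.8. These should be shown openly, with a note that an interval covering zero does not establish the absence of interaction.

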##### Cost-effectiveness

An economic evaluation will be conducted alongside the randomized trial and will be performed according to the intention-to-treat principle. Using a societal perspective, we will evaluate the relationship between costs, as measured with the TiC-P – and health outcomes of treatments at 9 months follow-up. A (secondary) health care perspective analysis will also be done. We will perform both a cost-effectiveness analysis with PTSD symptoms as effect measure and a cost-utility analysis using QALYs, based on the EQ-5D-5L.

### COVID-19 adjustments

Due to the COVID-19 outbreak in March 2020, the Jellinek treatment centers were entirely closed for new treatments for 6 weeks. During this time, inclusion of new participants was temporarily halted. The informed consent procedure and eligibility interview was conducted through video calling, however the baseline assessment was temporarily halted for participants who met the inclusion criteria. All assessments for patients that were already included were conducted by phone in line with lockdown restrictions. All included participants were informed about the changes in the procedure by a participant information letter about the modifications of the procedure. During these assessments an extra questionnaire on COVID-19 effects was temporarily included. This questionnaire consisted of 20 questions involving the effects of the Covid-19 outbreak on personal daily life and (mental) health. This questionnaire was designed by The Netherlands Study of Depression and Anxiety (NESDA) cohort study.

Patients in all treatment arms who had already started with treatment received the remainder of both their SUD and PTSD treatment through video calling during lockdown. No adjustments were made to the treatment protocols. For patients whose SUD treatment was postponed because of the COVID-19 measures, the PTSD treatment was also postponed until the COVID-19 measures were lifted and the SUD treatment as usual started.

Six weeks after the start of the first Covid lockdown new patients were included again, however they received their treatment as well as the assessments through video calling from the start. Baseline assessments also restarted, although measurements were done either by video calling or face-to-face.

When a range of lockdown measures lifted over the summer in 2020 and face-to-face sessions were possible again at the treatment center, all PTSD treatments were continued with face-to-face sessions. Since then, new participants all receive their entire treatment face-to-face at the location. However, when a therapist or patient is not allowed to come to the treatment facility center due to COVID-related symptoms, the session is delivered through video calling. For all sessions and assessments it is registered whether the session or assessment has been done by video calling or through a face-to-face session.

## Discussion

Completion of this RCT will provide more knowledge about the relative effectiveness of three treatment strategies for PTSD and their optimal timing in a population of patients with co-occurring SUD and PTSD. We will directly compare the effects of a PTSD treatment that is well-established for SUD nonetheless leads to high drop-out percentages (PE) and one treatment which is well-established for PTSD without SUD co-morbidity (EMDR) and one promising treatment for PTSD (ImRs). Furthermore, alcohol and drug use, treatment completion, psychological complaints, interpersonal problems, emotion regulation, trauma related emotions and cost-effectiveness of the three interventions will be examined. In addition, we will examine whether simultaneous or sequential treatment of SUD and PTSD is most effective.

### Methodological considerations

Strengths of this study are that we expect to include a cultural and socioeconomic diverse sample, since the participating centers are located in large cities and both intramural and extramural patients are included. A representative sample will be acquired by applying a minimum of exclusion criteria. The relatively long follow-up measurements of 9 months will provide insights in the long-term effects of the therapies. All therapists will be trained in all methods to prevent bias.

An important limitation of this study is the risks of high dropout rates at follow up measurements. Previous studies in this patient group have reported high assessment dropout rates [11]. We expect that patients might decide to drop out of the study once they hear they are allocated to a timing or type of treatment that differs from their personal preference. To limit this possibility, only disclosure of the timing will be given after randomization and disclosure of the treatment type will be done at the start of their first session of PTSD treatment, so that the therapist can motivate the patient for this kind of treatment. In addition, reminder calls are made before each assessment. Another limitation is that the power might be too low to detect small differences in effectiveness between types of PTSD treatment. Finally, due to the COVID-19 outbreak, temporarily adjustments in both treatment as well as measurements had to be made. Besides effects of these changes on measurements, there is possibly also a general effect of COVID-19 and the lockdown measures on the well-being of the participants. Therefore, at measurements during this period, it may be difficult to distinguish effects of treatment changes from general effects of this period.

### Conclusion

Patients with both PTSD and SUD have a high burden of disease. Currently, there is evidence that a simultaneous PE treatment is effective to treat PTSD in patients with co-occurring SUD, although effects are small, treatment dropout rates are high, and there is reluctance among therapists to offer PTSD and SUD treatment at the same time. Treatment guidelines for co-occurring PTSD and SUD can be improved based on the findings of this study, which may improve treatment outcomes of patients with this common comorbidity.

## Data Availability

The datasets and materials used or analyzed during this study will be available at the completion of this study from the corresponding author on reasonable request.

## Abbreviations

ACT: Acceptance and Commitment Therapy
AMC: Amsterdam academic Medical Center
AUDIT: Alcohol Use Disorder Identification Test
BSI: Brief Symptom Inventory
CAPS-5: Clinician Administered PTSD Scale for DSM-5
CBT: Cognitive Behavioral Therapy
CPTSD: Complex PTSD
CTQ-sf: Childhood Trauma Questionnaire-short form
DERS: Difficulties in Emotion Regulation Scale
DES: Daily Emotional Support subscale of the SSQT
DSM-5: Diagnostic and Statistical Manual of Mental Disorders
DUDIT: Drug Use Disorders Identification Test
EQ: EuroQol
EMDR: Eye Movement Desensitization and Reprocessing
(G)LMMs: (Generalized) Linear Mixed Models
IIP: Inventory of Interpersonal Problems
ImRs: Imagery Rescripting
ITQ: International Trauma Questionnaire
LEC-5: Life Events Checklist for DSM-5
MATE-Q: Meten van Addicties voor Triage en Evaluatie
MINI: Mini-International Neuropsychiatric Interview
NESDA: Netherlands Study of Depression and Anxiety
NTR: Nederlands Trial Register
PCL-5: PTSD Checklist for DSM-5
PE: Prolonged Exposure
PTSD: Post-Traumatic Stress Disorder
RCT: Randomized Controlled Trial
SCID-5-CV: Structured Clinical Diagnostic Interview for DSM-5 disorders – clinician version
SCL-90: Symptom Check List revised
SECS: Self Expression and Control Scale
SSQT: Social Support Questionnaire of Transactions
SSRI: Selective Serontonin Reuptake Inhibitor
SUD: Substance Use Disorder
TiC-P: Trimbos iMTA questionnaire for Costs associated with Psychiatric illness
TRGI: Trauma-Related Guilt Inventory
TOPA: Treatment Of PTSD and Addiction
TRSI: Trauma-Related Shame Inventory
WHO: World Health Organization
ZECV: Zelf Expressie en Controle Vragenlijst
